### Assignment of interventions: allocation

#### Sequence generation {16a}

Independent 1:1 random allocation to the two treatment arms will be used. This will be stratified by:
Wound location: foot and ankle, leg, abdomen or otherWound area (< 28 cm^2^, ≥ 28 cm^2^)Study centre

Stratification variables of wound location and wound area will be used as these have been found to impact on time to wound healing [8], whilst stratification by centre will be included to balance resource use across participating NHS Trusts. Variable blocks sizes will be used within strata.

For the recruitment SWAT, minimisation will be utilised to allocate sites based on the following factors: (i) whether the site is recruiting cross specialty or in a single specialty and (ii) expected number of eligible participants as reported on the site feasibility assessment cut at the median.

For the retention SWAT, participants will be allocated 1:1 using block randomisation stratified by host trial treatment arm, using randomly varying block sizes.

#### Concealment mechanism {16b}

Randomisation for the main trial will be completed by a centralised secure randomisation service hosted by York Trials Unit, University of York. Randomisation will be completed via the internet, with information recorded to check eligibility prior to randomisation.

#### Implementation {16c}

The allocation sequence for the main trial will be generated by the trial statistician who is independent to the recruiting teams at participating NHS Trust sites. This sequence will be implemented using the secure randomisation service that can be accessed by staff recruiting participants and will assign participants to either NPWT or standard care.

Similarly for the nested recruitment and retention SWATs, generation of the allocation sequence will be undertaken independently by a researcher not involved with the recruitment of participants.

### Assignment of interventions: blinding

#### Who will be blinded {17a}

As the study treatments cannot be adequately concealed, neither the trial participants nor the clinical care or research teams will be blinded to treatment allocation.

To limit potential bias in relation to primary outcome assessment, photographs taken of the wound following healing will be used to facilitate additional outcome (time to healing) verification by clinically experienced, independent, blinded observers.

For the two nested sub studies, as participants will not be informed of these methodological studies they will not be able to provide informed consent for their involvement and will therefore be blinded to their embedded trial allocation.

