### Outcomes {12}

#### Primary outcome

The primary outcome for SWHSI-2 is time to healing (defined using the clinical criterion “complete epithelial cover in the absence of a scab”) in days from randomisation.

Participants will be contacted weekly by a research nurse and asked if a healthcare professional has indicated that their wound has healed and whether this meets the healing definition (i.e. there is full coverage and no scab present). If the participant believes the wound is healed, but this has not been confirmed by a healthcare professional, the research nurse will seek confirmation/further information from the clinical team.

Once healing has been confirmed, participants will undergo clinical assessments on 3 subsequent consecutive weeks to confirm continued wound healing. A standardised photograph will be taken of the wound at the first healing assessment. Participants (with assistance from family/friends if necessary) will also be asked to take a digital photograph of the wound themselves and submit this to the study team. Study specific instructions will be provided to facilitate this.

Given the subjective nature of healing assessment (23), the photographs will be used to facilitate additional outcome (time to healing) verification by clinically experienced, independent, blinded observers.

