### Data collection and management

#### Plans for assessment and collection of outcomes {18a}

Data will be collected at baseline and at 3, 6 and 12 months post-randomisation, and via weekly clinical telephone follow-ups.

At baseline, epidemiological data will be collected including patient demographics, comorbidities, smoking status and surgical procedure details. Participants will complete a questionnaire comprising of a number of outcomes measures including surgical site infection (Bluebelle WHQ [17]), wound pain (using a visual analogue scale), quality of life (EuroQol EQ-5D-5L [19]) and resource use (using a bespoke, study specific questionnaire, which was designed based on the experiences learnt from the earlier feasibility study [27]).

At 3, 6 and 12 months, participants will be sent a postal questionnaire to complete and return comprising of a number of outcomes measures including surgical site infection (Bluebelle WHQ [17]), wound pain (using a visual analogue scale), health-related quality of life (EuroQol EQ-5D-5L [19]) and resource use (using a bespoke, study specific questionnaire). Where no response is provided after 2 weeks, a reminder questionnaire will be sent. If after 2 further weeks no response is received, a reminder telephone call will be made to the participant, and data collected by telephone if the participant is agreeable.

During the trial, participants will also be telephoned weekly to collect data on wound healing (using the criteria complete epithelial cover in the absence of a scab (eschar)), clinical events, treatment status and adverse events. When the participant reports that their treating healthcare professional has indicated that their wound is healed, and this has been confirmed in accordance with the SWHSI-2 trial definition (as above), the research nurse will undertake an assessment with the participant, ideally within 48 h of the report of healing being made, to confirm that the wound has healed. In the event wound healing has not been confirmed by a healthcare professional, the research nurse will first contact the clinical care team to obtain this confirmation and the date the participant was advised their wound was healed will be taken as the date of wound healing.

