When the wound is confirmed to be healed, clinical assessments will be completed with the participant on 3 consecutive weeks (commencing with the initial healing visit). At the initial visit a standardised photograph will be taken to facilitate blinded outcome verification, and the Bluebelle WHQ [17] will be completed. The research nurse will also determine whether surgical site infection (SSI) has occurred in the time since the participant has had an open surgical wound using a SSI reference assessment (Centre for Disease Control (CDC) criteria, assessed retrospectively. This CDC assessment is required as a reference assessment to enable validation of an SSI threshold score for the Bluebelle WHQ in patients with open surgical wounds.

Wherever possible the initial visit will be completed face to face at the participant’s home or in a clinical care setting to facilitate provision of the standardised photograph taken by the research nurse. Where this is not possible, a video call, using NHS approved technologies, will be arranged and a photograph taken via screen shot. If this is also not possible, the participant will be contacted by telephone and will be asked to take and to return (by electronic submission) a photograph of their wound. Subsequent healing visits (weeks 2 and 3) may then be completed by telephone, if preferred, to confirm continued wound healing.

At 12 months following randomisation, the research team will conduct a review of participants’ NHS medical records to identify and document any resources used, in relation to the participants wound, during the preceding 12 month period.

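### The blinded photographs can check healed status on the day of the photograph, but not the date of healing, and they cannot show that healing was declared late or never

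*Protocol article*

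**What the plan says.** Under Who will be blinded {17a}, "neither the trial participants nor the clinical care or research teams will be blinded to treatment allocation". To limit bias in assessing the primary outcome, the same section offers one blinded measure: "photographs taken of the wound following healing will be used to facilitate additional outcome (time to healing) verification by clinically experienced, independent, blinded observers". The Primary outcome section calls healing assessment subjective and repeats that the photographs serve to verify time to healing.

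Four other statements fix when the images arise:

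- **Standardised photograph.** "A standardised photograph will be taken of the wound at the first healing assessment" (Primary outcome).
- **Timing of that assessment.** Participants are telephoned weekly about healing. Once a report is made, the nurse assesses the wound "ideally within 48 h of the report of healing being made, to confirm that the wound has healed" (Plans for assessment and collection of outcomes {18a}).
- **Date recorded.** Where a professional had not yet confirmed healing, the nurse contacts the clinical team and "the date the participant was advised their wound was healed will be taken as the date of wound healing" ({18a}). For healing already declared by a professional, {18a} gives no separate rule. The statistical methods section counts days from randomisation to the first date of complete healing.
- **Other images.** A photograph is collected at baseline, with no stated role in verification. The Primary outcome section says that participants "will also be asked to take a digital photograph of the wound themselves and submit this to the study team", with no time given. {18a} mentions a participant photograph only where neither a visit nor a video call is possible: "the participant will be contacted by telephone and will be asked to take and to return (by electronic submission) a photograph of their wound". No photograph is described for the later checks: "Subsequent healing visits (weeks 2 and 3) may then be completed by telephone, if preferred, to confirm continued wound healing".

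**The concern.** The primary outcome is a time, and those who declare healing know the allocation. The bias to fear is therefore in when healing is declared: earlier in the favoured arm, or later in the other. The protocol describes its blinded check as one on time to healing. Yet the images linked to that check exist only after an unblinded declaration, and they postdate the date that is analysed.

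The check works in one direction. Readers can reject a declaration if the wound is still open when photographed. They have nothing to read for a wound that healed earlier than declared, or that was never declared healed. High agreement between readers and sites could therefore coexist with dates that differ by arm, and could be reported as support for unbiased timing.

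A later analysis plan cannot repair this alone, because it cannot supply images that were not taken.

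**Working it through.** **1. The plan's own figure.** Inputs from Sample size {14}: medians 86 and 65 days, 90% power, 12-month follow-up, 20% attrition; two-sided 5% from the statistical methods.

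- Hazard ratio for healing = 86/65 = 1.323.
- Schoenfeld events = 4 × (1.960 + 1.282)² / (ln 1.323)² = 536.2, so 537.
- Probability of healing by 365 days, exponential times: 1 − 2^(−365/86) = 0.947 and 1 − 2^(−365/65) = 0.980; mean 0.963.
- 537 / 0.963 = 557.4; 557.4 / 0.80 = 697, against 696 stated. The figure reproduces.
- Analysed per arm = 348 × 0.80 = 278.

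**2. Gap from recorded date to photograph.** If the date is the day of advice and this is learned at the next weekly call, the delay to the call is 0 to 7 days. The assessment adds up to 2 days if the 48 h target is met.

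- Nominal largest gap = 7 + 2 = 9 days; 9/21 = 43% of the 21-day target difference.
- Mean gap = 3.5 + 1 = 4.5 days if the visit falls evenly over the 48 h (4.5/21 = 21%), or 3.5 + 2 = 5.5 days if it is always at 48 h (5.5/21 = 26%).

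**3. What the photograph would catch.** Assume the call delay is uniform over 0 to 7 days. A wound dated d days too early still looks open in the photograph if its gap is shorter than d.

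| Dated early by | Visit uniform over 0–2 days | Visit fixed at 2 days |
|---|---|---|
| 4.5 days | 50% exposed | 2.5/7 = 36% exposed |
| 9 days | essentially 100% | essentially 100% |

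**4. The most early dating that passes every photograph.** Assume no true effect: median 86 days in both arms, exponential times, 278 per arm, censoring at 365 days. Each NPWT time is moved earlier by exactly that participant's own gap (floor 0.5 day), and usual care is left alone. Log-rank rejection at two-sided 5%, 20,000 simulated trials:

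| Scenario | Rejection | Apparent hazard ratio |
|---|---|---|
| No shift | 4.9% | 1.00 |
| Own gap, visit uniform over 0–2 days | 7.1% | 1.04 |
| Own gap, visit fixed at 2 days | 8.4% | 1.05 |

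**5. Late declaration, which no image checks.** The protocol gives no size, so 2 to 9 days in one arm is an assumption. Same model, 3,000 simulated trials:

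| Delay | Usual care late, no true effect: hazard ratio, rejection | NPWT late, design effect: hazard ratio, power |
|---|---|---|
| 0 days | 1.00, 4% | 1.33, 90% |
| 2 days | 1.02, 5% | not run |
| 7 days | 1.06, 11% | 1.24, 68% |
| 9 days | 1.08, 13% | 1.21, 59% |

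The delay to the photograph does not itself cause any of these shifts, because the photograph date is not the date analysed. They would arise only if declaration were delayed differently by arm.

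**The case against.** The strongest reply is that the photographs are offered only as additional help, on top of clinical assessment, and that other safeguards exist. There is a weekly enquiry, the nurse must seek confirmation when the participant believes the wound is healed, and healing is rechecked over three consecutive weeks. This stands as far as it goes, but all these steps are unblinded. The rechecks concern whether healing lasts, not when it occurred.

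The second reply is that 9 days is stated nowhere, and that the only explicit date rule belongs to the route where healing was not yet confirmed. On that route the advice may come after the call, so the 0 to 7 day part need not apply. This also stands. The figure is an inference, and because 48 h is only a target, it is not an upper limit either.

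The third reply is that adjudication rules may sit in an analysis plan or reader manual that is not shown. That covers how the readers' verdict is used. It does not cover which wounds are photographed and when, which this document fixes.

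Three stronger readings are tempting, and the protocol does not support them:

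- A reader might infer that NPWT healing could be dated a full 9 days early throughout and still pass. Step 3 shows that nearly all such images would reveal an open wound.
- A reader might infer that only one image per wound exists. That is true of the standardised photograph in follow-up, but participant and baseline photographs are also collected.
- A reader might infer that the blinded observers know every wound was declared healed. The protocol does not describe the reading set or what the observers are told.

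**Conclusion.** The point holds in a limited form. The photographs can confirm or refute healed status on the day they are taken, so premature declarations are partly checked. They cannot establish the date of healing, and as described they cannot reveal a late or missing declaration. Presenting them as verification of time to healing promises more than the scheme gives.

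Early dating that escapes every photograph raises the null rejection rate from 5% to about 7% to 8%. That requires the whole of one arm, and none of the other, to be misdated by the largest undetectable amount. It also rests on exponential times, calls spread evenly over the week and the 48 h target being met. If that target is missed, the gap and the undetected shift grow.

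Late declaration could matter more, since no image bounds it, but the figures in step 5 only illustrate assumed delays. Nothing in the protocol shows that either bias will occur.

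**What to change.** 1. In the Primary outcome and blinding sections, say that the photograph verifies healed status at the photographed assessment, not the date of healing.
2. Pre-specify a sensitivity analysis in which the event is dated at the photographed assessment that the blinded readers accept, so that date and evidence coincide. This deals with early dating only, because it still starts from an unblinded declaration.
3. Request the participant's own photograph when the participant first reports that the wound looks healed, whether or not the clinical team agrees, and include it in the blinded read. This gives some check on late declaration, though it still depends on an unblinded participant's report.
4. Reconcile the Primary outcome section with {18a} on whether the participant's photograph is routine or a fallback, and state when it is taken.

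The cost is protocol wording, one extra pre-specified analysis with dates a few days later in both arms, and somewhat more images for the same readers. The weekly contact exists already and the participant photograph is already planned. The sample size is unaffected. At the time of the article 252 of 696 participants had been recruited, so most could still be followed under the revised timing.

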#### Procedure for unblinding if needed {17b}

As study treatments cannot be blinded, there is no requirement for an unblinding procedure in this study.

Given the low risk of the nested sub studies, there is no requirement for an unblinding procedure for these components either.

### Data collection and management

#### Plans for assessment and collection of outcomes {18a}

Data will be collected at baseline and at 3, 6 and 12 months post-randomisation, and via weekly clinical telephone follow-ups.

At baseline, epidemiological data will be collected including patient demographics, comorbidities, smoking status and surgical procedure details. Participants will complete a questionnaire comprising of a number of outcomes measures including surgical site infection (Bluebelle WHQ [17]), wound pain (using a visual analogue scale), quality of life (EuroQol EQ-5D-5L [19]) and resource use (using a bespoke, study specific questionnaire, which was designed based on the experiences learnt from the earlier feasibility study [27]).

At 3, 6 and 12 months, participants will be sent a postal questionnaire to complete and return comprising of a number of outcomes measures including surgical site infection (Bluebelle WHQ [17]), wound pain (using a visual analogue scale), health-related quality of life (EuroQol EQ-5D-5L [19]) and resource use (using a bespoke, study specific questionnaire). Where no response is provided after 2 weeks, a reminder questionnaire will be sent. If after 2 further weeks no response is received, a reminder telephone call will be made to the participant, and data collected by telephone if the participant is agreeable.

During the trial, participants will also be telephoned weekly to collect data on wound healing (using the criteria complete epithelial cover in the absence of a scab (eschar)), clinical events, treatment status and adverse events. When the participant reports that their treating healthcare professional has indicated that their wound is healed, and this has been confirmed in accordance with the SWHSI-2 trial definition (as above), the research nurse will undertake an assessment with the participant, ideally within 48 h of the report of healing being made, to confirm that the wound has healed. In the event wound healing has not been confirmed by a healthcare professional, the research nurse will first contact the clinical care team to obtain this confirmation and the date the participant was advised their wound was healed will be taken as the date of wound healing.

When the wound is confirmed to be healed, clinical assessments will be completed with the participant on 3 consecutive weeks (commencing with the initial healing visit). At the initial visit a standardised photograph will be taken to facilitate blinded outcome verification, and the Bluebelle WHQ [17] will be completed. The research nurse will also determine whether surgical site infection (SSI) has occurred in the time since the participant has had an open surgical wound using a SSI reference assessment (Centre for Disease Control (CDC) criteria, assessed retrospectively. This CDC assessment is required as a reference assessment to enable validation of an SSI threshold score for the Bluebelle WHQ in patients with open surgical wounds.

Wherever possible the initial visit will be completed face to face at the participant’s home or in a clinical care setting to facilitate provision of the standardised photograph taken by the research nurse. Where this is not possible, a video call, using NHS approved technologies, will be arranged and a photograph taken via screen shot. If this is also not possible, the participant will be contacted by telephone and will be asked to take and to return (by electronic submission) a photograph of their wound. Subsequent healing visits (weeks 2 and 3) may then be completed by telephone, if preferred, to confirm continued wound healing.

At 12 months following randomisation, the research team will conduct a review of participants’ NHS medical records to identify and document any resources used, in relation to the participants wound, during the preceding 12 month period.

#### Plans to promote participant retention and complete follow-up {18b}

With the study primary outcome being time to wound healing, if participants wish to withdraw involvement from the trial, we will seek, where possible, consent to obtain data on healing status from the participant’s treating healthcare professional. This should ensure attrition of the primary outcome data is limited.

To ensure we are able to collect as much participant reported questionnaire data as possible, a range of strategies will be employed. Firstly, if there is no response to a postal questionnaire after 2 weeks, a reminder letter and questionnaire will be sent. If there is still no response after a further 2 weeks, the participant will be telephoned to collect their data. In addition, if for any reason a questionnaire cannot be posted to the participant, the study team may contact the participant by telephone in order to complete data collection. Secondly, participants will be sent a pen with each follow-up questionnaire and will receive an unconditional £5 with both the 6- and 12-month questionnaires. Both strategies have been found to have an effect in improving participant retention and questionnaire response rates [28–30]. Participants will also be sent a study newsletter 2 weeks before the 6-month follow-up time point to encourage continued engagement.

A SWAT testing a thank you card is also embedded within the SWHSI-2 trial. Participants will be individually randomised to either receive a thank you card at months four and nine following recruitment or to receive no thank you card at these time points.

Many recruitment and retention strategies routinely include some element of thanks within them; however, there is little to no evidence to suggest these work. There is therefore a need to test the impact of thanks in the context of trial retention.

#### Data management {19}

Participant data as required by the protocol will be recorded on case report forms (CRF). These will be completed at baseline, treatment delivery, weekly assessment, post wound healing and at 3, 6 and 12 months post-randomisation. Separate CRFs will be used to collect clinical information and patient reported information. Copies of the CRFs used in the trial are available as supplementary files.

To ensure high quality data, data collected within the CRFs will be processed at the York Trials Unit (YTU, University of York), using a licensed, automated, electronic system (Teleform), which allows data to be entered, checked and validated. Further details pertaining to the processing of the data will be documented in a study specific data management plan.

Study documentation will be retained in accordance with Good Research Practice and UK Law for five years after study completion in the Trial Master and Investigator Site Files, after which time information will be securely destroyed.

